#### 2.6.3. Classification of Outcome Scale for Evidence-Based GAS

It should define the classification of outcomes with the 5-level Likert scale after the setting of the goal of treatment to confirm the reliability and validity of results. The related discussion of the classification of outcomes is shown in Section 2.7. The criteria of assignment for every score should be described clearly. The score will be set as -2 if the outcome is far below expectation, −1 a little bit lower than expectation, 0 similar to expectation, 1 a little bit higher than expectation, and 2 higher than expectation. The definition of classification can be a behaviour, a state of emotion, a technique, or a process that reflects the goal. It also can be used as an indicator of progress in achieving the goal.

#### 2.6.4. Expected Results

The expected result of every goal is generally defined as the level 0 for the most likely to occur after treatment based on the 5-level Likert scale (Table 3), and the realization of the expected result will constitute a successful one. The expected result specified by the goal can be as accurate as possible through the detailed setting of every indicator.

#### 2.6.5. Realistic Results

Professional evaluators will assign corresponding scores according to the completion of each goal at the arranged time point after the therapy. *T* score will be calculated by the difference between the score of baseline and result based on the completion of evidence-based GAS. It will be the final score of a patient to evaluate the characteristics of clinical therapy. Two factors should be taken into account when calculating the score: (1) different weight scores (*w*_*i*_) should be given due to the different degrees of each indicator; (2) the influence of quantity variance should be eliminated due to the number difference of each goal. The formula is listed as follows:(1)$$\begin{array}{c} \text{GAS}=50+\frac{10\sum^{}\left(W_{i}X_{i}\right)}{\sqrt{\left(\left(1-p\right)\sum^{}w_{i}^{2}+p\left(\sum^{}w_{i}^{2}\right)\right)}}. \end{array}$$

Note: *x*_*i*_ represents the score for the indicator of the item *i*; *w*_*i*_ represents the weight for the indicator of the item *i*; *p*=0.3.

### 2.7. Outcomes

#### 2.7.1. Symptoms of Chest Pain

Symptoms of chest pain should be asked by physicians and replenished by family members. Symptoms should be around the frequency of attack, the degree, the duration, the location, the timing, the quality, and the accompanying discomforts which are related to the judgment of TCM syndrome. The discomforts should be on the basis of cold and heat, sweat, head and body, excrement, diet, and so on [15].

#### 2.7.2. Quality of Life

The information of the quality of life comes from the short-form health survey with 36 items (SF-36) [16], which is consisted as follows: (1) assessing physical functioning (PF; 10 items), (2) social functioning (SF; 2 items), (3) role limitation due to physical health (RP; 4 items), (4) bodily pain (BP; 2 items), (5) mental health (MH; 5 items), (6) role limitations due to emotional health (RE; 3 items), (7) vitality (VT; 4 items), (8) general health perceptions (GH; 5 items), and (9) reported health transition (1 item). We choose the item of 1 to 8 for the evaluation of the quality of life.

#### 2.7.3. Situations of Drug Use

The drug contains the application of TCM and western medicine. The situation of drugs for TCM and western medicine will be measured by types, dosage, frequency, duration, and side effects. It should be highlighted that the reasons for the change of drug should be recorded clearly. The application of drugs should follow the medical advice of doctors strictly.

#### 2.7.4. Financial Burden

The financial burden is an essential part of patients [17]. The financial burden of patients will be evaluated from the direct burden, the indirect burden, and the invisible burden [18]. The direct burden will be measured by the payments for health services. The indirect burden will be measured by the loss of social and family values due to the disease. The invisible burden will be measured by the decrease in quality of life due to disease.

#### 2.7.5. Prognosis of Patients

The prognosis of patients will be asked by the report of major adverse cardiovascular events (MACEs) [19], which are listed as follows: (1) cardiovascular cause of death. The attribution of death should be in the subcategories of acute myocardial infarction, sudden cardiac death, heart failure, stroke, cardiovascular procedure, and cardiovascular haemorrhage. (2) Myocardial infarction (MI). Its diagnosis is based on cardiac troponin and the MB fraction of creatine kinase (CK-MB) [20]. (3) Stroke. It is defined on the basis of the presence of acute infarction as demonstrated by imaging or the persistence of symptoms. (4) Transient ischemic attack (TIA). It is the transient episode of focal neurological dysfunction caused by the brain, spinal cord, or retinal ischemia [21]. (5) Percutaneous coronary intervention (PCI). The stents can be the new classification named drug-coated balloons and bioresorbable drug-eluting stents/scaffolds. (6) Peripheral vascular intervention. The concentrated area of it includes the infrarenal aorta, iliac, and infrainguinal arteries and carotid, renal, mesenteric, and aortic interventions. (7) Rehospitalization: this is due to cardiovascular events.

#### 2.7.6. Physical and Chemical Indicators

The indicators including 7 categories will be measured as follows: (1) blood lipid: cholesterol (CHO), triglycerides (TG), high-density lipoprotein (HDL), and low-density lipoprotein (LDL). (2) Vascular endothelial function: C-reactive protein (CRP), nitric oxide (NO), and endothelin (ET). (3) Blood rheologic indexes: erythrocyte sedimentation rate (ESR). (4) Oxidative stress: malondialdehyde (MDA) and superoxide dismutase (SOD). (5) Myocardial injure marker: creatine kinase-MB (CK-MB), creatine kinase (CK), cardiac troponin T (cTnT), cardiac troponin I (cTnI), and lactate dehydrogenase (LDH). (6) Liver and kidney functions: aspartate aminotransferase (AST), alanine aminotransferase (ALT), albumin (ALB), blood urea nitrogen (BUN), and serum creatinine (SCR). (7) Blood coagulation factor: prothrombin time (PT), activated partial thromboplastin time (APTT), thrombin time (TT), and fibrinogen (FIB).

#### 2.7.7. Imaging Indexes

The indexes will be collected and inquired including echocardiography (left ventricular ejection fraction, LVEF), chest radiography, chest tomography (CT), and magnetic resonance imaging (MRI).

#### 2.7.8. Efficiency of TCM Syndrome

The efficiency will be evaluated on the basis of the degree of TCM syndrome improvement before and after therapy [13]. The corresponding adjustment is conducted to adopt the 5-level Likert scale of evidence-based GAS. The standard table of TCM syndrome score is calculated as follows: decrement rate of syndrome score (efficacy index %) = [(score of pretreatment − score of posttreatment)/score of pretreatment] × 100%. Enormous amelioration represents the percentage reduction of syndrome score ≥ 90%; obvious amelioration represents the percentage reduction of syndrome score ≥ 70% and ＜90%; a little bit amelioration represents the percentage reduction of syndrome score ≥ 30% and ＜70%; no obvious variation represents the percentage reduction of syndrome score < 30%; obvious aggravation represents the percentage reduction of syndrome score < 0 (Table 3).

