## Figures and Tables

**Figure 1 fig1:**
[figure not shown]
Flow diagram of observational research by the evidence-based Goal Attainment Scale.

**Table 1 tab1:** The classification of score of weight for *Importance* and *Difficulty*.

Importance	Difficulty
0 = not important	0 = not difficult
1 = slightly important	1 = slightly difficult
2 = important	2 = difficult
3 = very important	3 = very difficult

**Table 2 tab2:** The goal of treatment from physicians and evidence-based medicine (3 to 5 goals among the 8 goals can be selected form the table).

Goal of treatment	Importance	Difficulty	Weight	Baseline	Results
1. Whether can improve the symptom of chest pain					
2. Whether can improve the quality of life (based on the SF-36 form)					
3. Whether can reduce the drug use					
4. Whether can reduce finical burden of patients					
5. Whether can improve prognosis of patients based on the report of MACE					
6. Whether can improve the physical-chemical indexes (blood lipids, vascular endothelial function, blood rheologic indexes, oxidative stress, blood routine, liver and kidney functions, and blood coagulation factor)					
7. Whether can improve imaging indexes (LVEF, chest radiography, CT, and MRI)					
8. Whether can improve syndrome efficiency of TCM					
9. Handwritten: the first goal of treatment that patients they want					
10. Handwritten: the second goal of treatment that patients they want					
*Sum of weight*					

**Table 3 tab3:** Scale for evidence-based GAS.

Scale for evidence-based GAS	−2	−1	0	1	2
					
1. Symptom of chest pain	Increase of the frequency of attack and the degree of pain, prolong for duration	No change of the frequency of attack, the degree of pain, and duration	A little bit relieves of the frequency of attack, the degree of pain, and duration	Obvious relieves of the frequency of attack, the degree of pain, and the duration	No any symptoms of chest pain

2. Quality of life based on SF-36 (^1^physiological function, ^2^physical function, ^3^body pain, ^4^general health, ^5^vitality, ^6^social function, ^7^emotional function, and ^8^mental health)	Aggravate obviously for 2 or more among the 8 dimensions of SF-36	No clearly improvement among the 8 dimensions of SF-36	Obvious amelioration for 1 to 2 among the 8 dimensions of SF-36	Obvious amelioration for 3 to 4 among the 8 dimensions of SF-36	Obvious amelioration for more than 4 among the 8 dimensions of SF-36

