3. Situations of drug use	Obvious increase of dosage and categories	No obvious variations for dosage and categories	Decrease of dosage and categories (1 to 2)	Obvious decrease of dosage and categories (more than 2)	Discontinue drug followed by the doctor's advice

4. Financial burden	Obvious increase of financial input	No obvious change of financial input compared with before	Decrease of financial input and relieve of the burden	Obvious decrease of financial input and relieve of the burden	No financial burden

5. Prognosis of patients (MACE: ^1^death, ^2^MI, ^3^stroke, ^4^TIA, ^5^PCI, ^6^peripheral vascular intervention, and ^7^readmission)	1 or more new events (MACE) report compared with before	Events were observed similar to before and no new events report	No event (MACE) reports	No event (MACE) reports for a long time (six months to one year)	No event (MACE) reports for a long time (more than one year)

6. Physical and chemical indicators (^1^blood lipid, ^2^vascular endothelial function, ^3^blood rheologic indexes, ^4^oxidative stress, ^5^myocardial injure marker, ^6^liver and kidney functions, and ^7^blood coagulation factor)	Obvious aggravated more than 2 indicators	No obvious change compared with before	Amelioration of 1 to 2 indicators compared with before	Amelioration of 3 to 4 indicators compared with before	Amelioration of more than 4 indicators compared with before

7. Imaging indexes (^1^LVEF, ^2^chest radiography, ^3^CT, and ^4^MRI)	Obvious aggravated more than 2 indexes	No obvious change compared with before	Amelioration of 1 to 2 indexes compared with before	Amelioration of 2 to 3indicators compared with before	Amelioration of more than 3 indicators compared with before

8. Efficiency of TCM syndrome [13]	Obvious aggravated of the TCM syndrome compared with before	No obvious variation of the TCM syndrome compared with before	A little bit amelioration of the TCM syndrome compared with before	Obvious amelioration of TCM syndrome compared with before	Enormous amelioration of TCM syndrome compared with before

9. Handwriting: the goal 1 that patients want to achieve)					

10. Handwriting: the goal 2 that patients want to achieve					

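### Several goal-attainment levels overlap or leave gaps, so the syndrome, imaging, laboratory and SF-36 goals can give one patient two scores or none

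*Protocol article*

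**What the plan says.** All references are to the protocol article.

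- **Syndrome (Section 2.7.8).** The two lowest bands are "no obvious variation represents the percentage reduction of syndrome score < 30%; obvious aggravation represents the percentage reduction of syndrome score < 0". The band above them starts at "a little bit amelioration represents the percentage reduction of syndrome score ≥ 30" per cent and is closed at 70%.
- **Imaging (Table 3, item 7; four indexes).** Level 0 is "Amelioration of 1 to 2 indexes compared with before", level +1 is "Amelioration of 2 to 3indicators compared with before" and level −2 is "Obvious aggravated more than 2 indexes".
- **Laboratory (Table 3, item 6; seven numbered categories).** Level −2 is "Obvious aggravated more than 2 indicators" and level 0 is "Amelioration of 1 to 2 indicators compared with before". For both laboratory and imaging, level −1 is the absence of any obvious change.
- **SF-36 (Table 3, item 2; eight dimensions).** Level −2 is "Aggravate obviously for 2 or more among the 8 dimensions of SF-36". Level −1 is no clear improvement. Levels 0, +1 and +2 are obvious improvement in 1 to 2, 3 to 4 and more than 4 dimensions.

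Section 2.6.2 sets baseline at −1 in general. Section 2.6.4 treats reaching level 0 as success. Section 2.6.3 asks that the criteria for each score be clear. Section 2.4 states that there is no control group. Section 2.9 analyses the goal-attainment results over time by repeated-measures ANOVA.

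**The concern.** A five-level scale works only if every possible patient state maps to exactly one level. Read literally, four of the eight preset goals fail this test: some states meet two levels and others meet none. The evaluator must then choose, and two evaluators can score the same findings differently.

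The laboratory and imaging wording is also uneven. Leaving −1 upwards needs amelioration of one indicator, with no size stated. Leaving it downwards needs obvious worsening of more than two.

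The study is a before-after comparison, so there is no second arm in which a lenient or inconsistent scoring habit would cancel. The usual baseline sits one level below success, so a one-level choice at that boundary decides whether the goal counts as attained.

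**Working it through.** The article gives no error rate or other figure for this point, so there is nothing to reproduce. The check has three steps.

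**1. Code each level literally and list the states.** Let *i* be the number of indicators improved and *w* the number worsened, with *i* + *w* no larger than the number of indicators.

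| Goal | States (i, w) | Meet two levels | Meet none |
|---|---|---|---|
| SF-36 (8 dimensions) | 45 | 28 | 0 |
| Laboratory (7 categories) | 36 | 10 | 2 |
| Imaging (4 indexes) | 15 | 4 | 2 |

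- Syndrome: a reduction of −1% or of −50% meets both −1 and −2. Values of 0% and above meet one level each.
- Imaging: *i* = 2 meets 0 and +1 whatever *w* is (three states). One better with three worse meets 0 and −2 (the fourth).
- SF-36: every state with *w* ≥ 2 is double. Two worse and none better meets −2 and −1. Two worse with 1 to 2, 3 to 4 or 5 to 6 better meets −2 together with 0, +1 or +2.
- Laboratory: three or more worse with one to four better meets −2 together with 0 or +1.
- Gaps: laboratory and imaging with *i* = 0 and *w* = 1 or 2.

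**2. Size of one level on T.** The formula in Section 2.6.5 has the sum of squared weights in both terms under the root, so *p* drops out. With *k* equally weighted goals, one level on one goal moves T by 10/√k:

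- k = 3: 5.8
- k = 4: 5.0
- k = 5: 4.5

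The widest conflict, SF-36 at −2 or +2, is four levels: 4 × 4.47 = 17.9 to 4 × 5.77 = 23.1 points.

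**3. Illustration of noise.** Assume no true change, independent indicators, and a probability *q* that each is called improved (and the same *q* that it is called obviously worse). *q* is not in the article; 5% and 10% are used.

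The chance of qualifying for level 0 or better is 1 − (1 − q)^n:

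- Laboratory, n = 7: 1 − 0.95^7 = 30.2%; 1 − 0.90^7 = 52.2%
- Imaging, n = 4: 1 − 0.95^4 = 18.5%; 1 − 0.90^4 = 34.4%
- SF-36, n = 8: 1 − 0.95^8 = 33.7%; 1 − 0.90^8 = 57.0%

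The chance of falling in a gap is nq(1 − 2q)^(n−1) + C(n,2)q²(1 − 2q)^(n−2):

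- Laboratory: 21.7% and 25.2%
- Imaging: 15.8% and 24.3%

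The chance of qualifying for −2 in the same model:

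- SF-36: 5.7% and 18.7%
- Laboratory: 0.4% and 2.6%
- Imaging: at most 0.4%

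If the worse level is always taken and gaps are scored −1, the mean at q = 10% is −0.49 (laboratory), −0.66 (imaging) and −0.67 (SF-36). All three lie above the usual baseline of −1.

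**The case against.** The strongest reply is that most of this is loose wording that a sensible evaluator would resolve. The syndrome bands form a descending cascade, and the natural reading takes the below-zero band out of the below-30% band. That is fair, and it makes syndrome the easiest conflict to repair, but the text does not say it. No such reading settles two improved imaging indexes or mixed change on SF-36.

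Each patient has only three to five goals, so a given conflict affects only patients who chose that goal and landed in that state. This stands and limits the reach of each item.

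Four stronger readings are tempting, and the article does not support them.

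- **That noise scores as improvement on all four goals.** For syndrome the opposite holds: improvement needs a 30% reduction, while any rise can count as −2.
- **That the laboratory and imaging rules push an unchanged patient to success.** Level −1 for both goals covers no obvious change, so trivial drift can be scored there. Counting every upward movement as amelioration (q = 50%) nearly empties that level. It would also give a 99/128 = 77% chance of more than two of seven categories worse, so most such patients would qualify for −2 as well.
- **That laboratory indicators are the 24 single tests of Section 2.7.6.** Table 3 numbers seven categories, and that is the better-supported unit.
- **That the evaluators are known to be unblinded.** Section 2.6.5 says only that they are professional. Blinding is not described either way.

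**Conclusion.** The point holds as a defect in stated rules, not as missing detail. The levels for syndrome, imaging, laboratory and SF-36 are not mutually exclusive, and those for laboratory and imaging are also not exhaustive. This falls short of the article's own requirement of clear criteria. It needs no assumption and should be settled before any patient is scored.

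The size of one conflict rests on equal weights, three to five goals and the printed formula. The noise percentages are illustrative: they depend on *q* and on independence, which related tests within a patient will not fully satisfy. They show how often level 0 becomes available without true change, not how often it would be awarded. The article does not allow the resulting bias in the mean score to be estimated, because it gives no precedence rule and no numerical meaning for an obvious change.

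**What to change.** **Syndrome.** Level −1 is a reduction of 0% to below 30%; level −2 is a reduction below 0. A wider margin for −2, such as −30%, should not be added alone, because reductions from −30% to 0 would then have no level.

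**SF-36, laboratory and imaging.** Score the net count (obviously improved minus obviously worsened), with the same definition of obvious in both directions. For laboratory, an indicator is one of the seven categories in Table 3.

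| Level | SF-36 | Laboratory | Imaging |
|---|---|---|---|
| −2 | ≤ −2 | ≤ −3 | ≤ −3 |
| −1 | −1 or 0 | −2 to 0 | −2 to 0 |
| 0 | 1 to 2 | 1 to 2 | 1 |
| +1 | 3 to 4 | 3 to 4 | 2 to 3 |
| +2 | ≥ 5 | ≥ 5 | 4 |

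Every net count now maps to one level, and the article's own counts are kept except at the imaging overlap. The rule does not remove noise: one falsely improved indicator with none worse still scores 0. The threshold for obvious should therefore be stated in numbers, including when a category with several tests counts as changed.

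The cost is an edit to Section 2.7.8, Table 3 and the case report form before scoring. Patients with mixed change will score somewhat less favourably than if the better level were taken.

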### 2.8. Adverse Events

#### 2.8.1. Definition of Adverse Events

This definition contains the appearance or deterioration of any syndrome, symptom, or disease that may affect the health of patients during the observation period. The adverse events can be new diseases, deterioration of symptoms, treatment, or disease, and a combination of one or more factors, which does not represent the direct causal relationship with the individualized treatment of TCM.

#### 2.8.2. Serious Adverse Events

These events include death, life-threatening events, prolonged hospitalization, disability, congenital malformation, crucial medical events (events that may not immediately endanger life or result in death or hospitalization but may endanger the patient or require action to prevent consequences mentioned above), and medical treatment to prevent permanent damage.

#### 2.8.3. Judgment between Adverse Events and Drugs

(1) Whether there is a reasonable relationship between the time of TCM individualized treatment and suspicious adverse reactions. (2) Whether the suspected adverse reactions are consistent with types of adverse events that are already known for TCM individualized treatment. (3) Whether suspected adverse reactions can be reduced and disappear on the basis of drug withdrawal and dosage reductions. (4) Whether the same reaction occurs again after using the same drug. (5) Whether the suspected adverse reactions can be explained by the pathological status, combination of drugs, and previous therapy of patients.

#### 2.8.4. Management of Adverse Event Researchers

The variation of the condition of patients should be recorded for individualized TCM treatment faithfully. Adverse reactions or unexpected toxic side effects (including symptoms, signs, and laboratory indicators) should be paid attention during the evaluation of the efficacy with the evidence-based GAS. The symptoms, degree, occurrence time, duration, and measures of adverse reactions during hospitalization and follow-up should be recorded in the questionnaire and marked with the date.

### 2.9. Statistical Analysis

The software SPSS version 19.0 will be used for statistical analysis. All statistical analysis will be in the significance level 0.05 and expressed by the 95% confidence interval (CI) or two-sided test. The description of quantitative indicators for baseline and the demographic feature will calculate the mean, standard deviation, median (distributed data), and maximum (distribution data). The description of qualitative indicators will calculate the frequency and percentage. Results of evidence-based GAS on different times will be analysed by the repeated measures ANOVA to observe the dynamic characteristics of individualized curative effect. Among the repeated measures ANOVA, the multivariable test (Pillai's trace, Wilks' lambda, Hotelling's trace, and Roy's largest root) will be used to judge the difference of efficiency at different time points; Mauchly's test of sphericity will be applied to determine whether the corrected test (Greenhouse–Geisser, Huynh–Feldt, and lower-bound) is needed; tests of within-subjects effects will be judged whether the result is consistent with the multivariable test; tests of within-subjects contrasts will evaluate whether the change of curative effect was in accordance with the form of the curve; tests of between-subjects effects will be used to determine whether the efficacy of pairwise comparison at each time point was statistically significant.

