### 2.2. Study Setting and Trial Design

This is observational research which will conduct at the Dongzhimen Hospital Affiliated to Beijing University of Chinese Medicine (BUCM), the Third Affiliated Hospital of BUCM, and the Beijing Hospital of Traditional Chinese Medicine Affiliated to Capital Medical University. This research has a prospective feature, which means that the admission period of patients will be between March 1, 2020, and August 31, 2020. We will include 200 hospitalized patients who were diagnosed as NSTE-ACS. Each included patient will be followed up by telephone or door visit every 2 weeks, collecting the individualized intervention of TCM and evaluating through the table of evidence-based GAS. The whole procedure of the research will consist of 6 times of follow-up. This protocol conforms to the statement of Strengthening the Reporting of Observational Studies in Epidemiology (STROBE) [11] (see Supplementary File 2) and is made some adjustments based on the adaptability for TCM.

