### 2.4. Interventions

This protocol is the observational setting with no controlled group. The method of self-control is used to compare therapeutic efficiency. All included participants will not apply any particular interventions for the aim of scientific research. The tool of evidence-based GAS is the way of analysis and evaluation, which represents patients who can receive the individualized treatment of TCM or western medicine based on their situations. The only requirement is they should choose the TCM or combined therapy if they have a need to be treated by physicians.

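### Section 2.9 tests pairwise visit differences and curve contrasts at a blanket 0.05 with no stated gate or adjustment; unadjusted pairs give about a 32–38% chance of a false visit-to-visit difference over six follow-ups, and gating alone does not cure it.

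*Protocol article*

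**What the plan says.** Section 2.9 of the protocol article fixes the level for every analysis: "All statistical analysis will be in the significance level 0.05 and expressed by the 95% confidence interval (CI) or two-sided test". Within the repeated measures ANOVA of the GAS score it then gives each test a task:

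- The multivariate test (four statistics) "will be used to judge the difference of efficiency at different time points".
- On the within-subjects test: "tests of within-subjects effects will be judged whether the result is consistent with the multivariable test".
- On curve shape: "tests of within-subjects contrasts will evaluate whether the change of curative effect was in accordance with the form of the curve".
- On pairs of time points: "tests of between-subjects effects will be used to determine whether the efficacy of pairwise comparison at each time point was statistically significant".

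On the number of time points, Section 2.2 says: "The whole procedure of the research will consist of 6 times of follow-up". Section 2.4 confirms a single group: "This protocol is the observational setting with no controlled group". Section 2.6.2 sets the baseline level of each goal by rule, usually −1 and sometimes −2. Section 2.6.5 describes the T score as a difference between baseline and result. The article does not say whether baseline is a level of the time factor.

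**The concern.** The study has no control group and aims to describe how the treatment effect moves over time. Statements that the effect differs between particular visits are therefore a main product, and they come from the pairwise and curve tests. There are many of these, and the only stated rule is 0.05 for each analysis. Nothing says that they wait for a significant overall test or that their p values are adjusted. The within-subjects test is to be checked for consistency with the multivariate test, with no rule for disagreement.

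At stake is how a reader should take a statement that the score at one visit differed from the score at another. If any of 15 or more unadjusted comparisons may support it, such a statement will often appear when the visits do not differ.

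**Working it through.** The plan states no familywise error rate, so there is no planned figure to reproduce. The check asks how often at least one truly null comparison falls below 0.05.

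**Inputs from the article:** two-sided 0.05 (2.9); six follow-ups (2.2); one group (2.4); 200 patients (2.5). **Assumed:** normal scores; within-patient correlation either exchangeable (0.3, 0.6, 0.8) or AR(1) (0.5, 0.7, 0.9); no missing visits.

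**1. Number of tests.** Pairs = k(k−1)/2 and polynomial contrasts = k−1.
- k = 6 (follow-ups only): 6×5/2 = 15 pairs, 5 contrasts.
- k = 7 (baseline included): 7×6/2 = 21 pairs, 6 contrasts.

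With one group and one outcome the four multivariate statistics give the same F test, so they count once.

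**2. Closed-form check for all pairs, no change at any visit.** Under equal correlation and a large sample, at least one pair reaches |z| > 1.96 when the standardized range of k means exceeds 1.96×√2 = 2.77. The studentized-range tail gives 36.6% for k = 6 and 44.0% for k = 7. Treating the 15 tests as independent gives 1 − 0.95^15 = 53.7%, which is too high because the pairs share visits.

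**3. Simulation, no change at any visit** (n = 200, paired t tests, 6,000 runs per setting, including one run with scores rounded to −2…2):

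| At least one p < 0.05 | 6 levels | 7 levels |
|---|---|---|
| Any pair, unadjusted | 32–38% | 38–46% |
| Any curve contrast | 22–23% | 26–28% |
| Any pair, contrast or overall test | 36–40% | 43–48% |
| Overall multivariate test alone | 4.8–5.5% | 4.5–5.6% |
| Pairs and contrasts read only if the overall test is significant | 4.8–5.5% | 4.5–5.6% |
| Any pair, Bonferroni | 3.2–4.4% | 2.8–4.4% |

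Six comparisons with baseline only, with baseline varying like a visit, give about 18–21%. The lowest setting, AR(1) 0.9, gives 16.5%.

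**4. Does gating on the overall test solve it?** It does only when nothing changes at any visit. Suppose the score rises early and then stays flat. The overall test is then rightly significant, and the plateau visits are still compared at 0.05 each.

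- Baseline constant, 1 SD gain, plateau over all six follow-ups: gate open in 100% of 3,000 runs. A false plateau difference appears in 36.4% (exchangeable 0.5) and 34.8% (AR(1) 0.7).
- Baseline varying like a visit, 1 SD gain by the first follow-up, then plateau: gate open in every run; false difference in 32–37%.
- Six follow-ups only, 0.5 SD gain from visit 1 to visit 2, then plateau: gate open in 100%; false difference in 29.1% and 25.8%.

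The closed form agrees. Once the gate is open, the rate is the range formula for the plateau visits: 36.6% for six, and 28.6% for five (k = 5 in step 2). Holm over all pairs held 3.8–4.4% in the first and third of these settings.

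**The case against.** A reader might infer that the trial's efficacy claim carries a flat 30–45% false-positive risk. The article does not support that. Section 2.9 gives the multivariate test the job of judging differences over time, and if nothing changes at any visit that test holds about 5%. So does any pairwise or curve result read only after it. The large figures need a single pairwise result to carry a claim on its own, which the text permits but does not state. The same wording makes the multivariate test the reference for the within-subjects test. Only the rule for disagreement is missing.

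Further points stand:

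- The number of pairs is inferred. The text assigns pairwise comparison to between-subjects tests, which do not compare time points in a single group. The counts of 15 or 21 assume that this is corrected.
- The seven-level figures treat baseline as free to vary, while Section 2.6.2 sets it by rule. Six levels fit the text better.
- A 0.05 level is compatible with adjusted p values, and an article may leave the adjustment to a fuller document.
- The study is observational and rates its own evidence as low level, so strict familywise control of a visit profile is partly a matter of judgement.

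What does not stand is the view that the overall test is protection enough. It protects only when no visit differs from any other, and an early gain followed by stability is a plausible course. The gain sizes in step 4 are assumptions, but they matter only in being large enough to open the gate.

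**Conclusion.** The concern holds in limited form. Section 2.9 states 0.05 for every analysis and lists pairwise and curve tests without a gate or adjustment. For six follow-ups, unadjusted and ungated pairs give about a 32–38% chance of at least one false visit-to-visit difference. The figure is about 38–46% with baseline as a freely varying seventh level and about 18–21% for the six baseline comparisons alone. Gated on the overall test, the rate is about 5% if nothing changes at any visit, but about 26–37% after an early gain and a plateau.

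These are rates for false statements about particular visits. They are not the error rate of the overall test, which is sound. Nor does the article give grounds for one particular visit as the deciding one, or for dropping the multivariate test. The figures rest on normal scores, complete follow-up, assumed correlations and an inferred number of pairs.

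**What to change.** In Section 2.9:

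1. Keep the multivariate test as the overall time test at 0.05, and state that it decides if the within-subjects test disagrees.
2. State whether baseline is a level of the time factor. Report the pairwise time-point comparisons, taken from within-subject comparisons, with Bonferroni- or Holm-adjusted p values (SPSS offers Bonferroni and Sidak). Alternatively, restrict them to the comparisons with baseline, with the same adjustment.
3. Label the curve contrasts descriptive.
4. Naming one deciding time point in advance is advisable; which one is the investigators' choice.

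The cost is wording and one software option, with no extra patients or data. The price is sensitivity: the strictest step becomes 0.05/15 = 0.0033 for six levels, 0.05/21 = 0.0024 for seven, or 0.05/6 = 0.0083 for baseline comparisons only. Small differences between adjacent visits are then less likely to be called significant. The overall test, and any single time point named in advance, keep the full 0.05.
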